**Methodology:**

1. Study Design

A randomized, double-blinded, controlled, parallel group, repeated-measures design will be used. Ethical approval will be obtained from The Hong Kong Polytechnic University and Caritas Institute of Higher Education. The trial will be conducted in accordance with the Declaration of Helsinki.

1. Study subjects

Based on the effect sizes from previous relevant studies, the sample size has been calculated and 90 patients with KOA will be recruited from the general public with the physiotherapy referral from a doctor with the diagnosis of KOA and screened by knee X-ray with the Kellgren and Lawrence (KL) scale (Petersoon et al., 1997). Their age, gender, body mass index (BMI), unilateral or bilateral knees involved, duration of knee pain and any history of knee injury will be recorded as baseline information. The current study targets in mild to moderate degenerative KOA with XR showing with the KL scale (Petersoon et al., 1997) grade I and grade III (which is most beneficial to conservative treatment) (Appendix III). KL scale was proposed in 1957 and accepted by the WHO in 1961, it has been widely used in grading the severity of KOA (Samuel & Kanimozhi, 2019). All the classification of XR with the KL scale in this study will be done by a physiotherapist who has more than 10 years experience in musculoskeletal conditions and training in interpretation of knee XR with the classification of KL scale. All the subjects meet the inclusion criteria will be allocated by computer randomized program that will be created by a statistician who is not otherwise involved in the trial and does not participate in analysis or interpretation of the results. The allocation sequence will be concealed from the principal investigator enrolling and assessing participants as each participant’s allocation which will be contained in sequentially numbered sealed and stapled opaque envelopes. All the eligible subjects will be allocated into G1, G2, and G3. Each group will recruit 30 subjects. The assessor will be blinded to the patient’s treatment group assignment at all time and will carry all the baseline, 4-week and 8-week evaluations.

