Assessed for eligibility with inclusion and exclusion criteria

Obtaining written consent

Randomized with computer program by an independent statistician and the allocation sequence will be concealed with sealed and stapled opaque envelopes

Baseline assessment

G2

DN with placebo US-guide+

supervised exercise, exercise pamphlet and educational video

G1

DN + real US-guide+ routine supervised exercise and exercise pamphlet, educational video

G3

Control from waiting list without any treatment

Follow up immediate after the last session at the 4-week and 8-week follow-ups, and data analysis and post intervention analysis with mixed model ANOVA

1. Sample Size and rational for calculation

The effect size is calculated by using G-Power version 3.1.9.4 (Franz Faul, Universität Kiel, Germany)

With reference previous similar study of using acupuncture on KOA (Williamson et al., 2007), the effect size of VAS is set as 0.339 for the VAS, power as 0.8, level of statistical significance as 0.05. The number of subjects estimated for each group will be 26; total number of subjects was 78.

1. Method of data analysis:

Statistical analyses will be performed on the Intention to treat (ITT) population, including all randomized participants. Missing data will be replaced using multiple imputation (5 iterations). Intention to treat (ITT) analysis will be used in the data analysis. The data will be analyzed by using mixed model analysis of variance (ANOVA) (two-tailed) with ‘time’ as the within subjects factor (Baseline, 4 weeks and 8 weeks after treatment), whereas the ‘group’ factor will be analyzed for the between groups differences (G1, G2 and G3). The significant level will be set at 0.05 and bonferroni correction will be applied. Wilks’ Lambda will be used for statistic significance analysis. The assumption of sphericity will be tested by the Mauchly’s test and the assumption of normality will be tested by the Shapiro-Wilk test. Post hoc analysis by will be conducted if significant difference is found in the corresponding outcomes measures so as to identify the difference amongst the comparisons between groups. All statistical analysis will be conducted using SPSS version 23 (IMB, SPSS) and all analyses will be processed blind to identify of treatment groups by an independent research assistant.

1. Details of procedure of applying US-guided DN

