2. Knee injury and Osteoarthritis Outcome Score (KOOS)-short form is validated to be used in KOA patients (Lyman et al., 2016). KOOS is a valid, reliable and responsive outcomes measure, and it can improve the validity as compared with WOMAC (Roos et al., 2003). The Chinese translated version of KOOS is a reliable and valid instrument for OAK patients and showed fairly strong association with WOMAC (Cheung, Ngai and Ho., 2016). As WOMAC requires license and cost, KOOS is free to be used, KOOS already has been commonly used as a functional outcomes in most public hospitals in Hong Kong for KOA patients. The KOOS-short form involves three domains including pain, symptoms and quality-of-life (QoL). The score from ‘0’ to ‘4’ indicated none to severe and then the KOOS pain score can be calculated with the following formula:

KOOS-pain= 100 – (mean score of pain domain x 100)/4

The values of KOOS-subscales (symptoms and QoL) can be assessed by the above formula.

1. Evaluation of the Validity of placebo method

This study involves US-guide and stated clearly in the consent form and information sheet provided to very subjects. If one the study group does not provide US-guide, they may know that they are not allocated into the intervention group. To avoid the bias and potential placebo effect from US-guide, it is necessary to blind the subjects during the procedure of US-guide DN. All the subjects in G1 and G2 will receive either real-US-guide or placebo US-guide with US monitor’s screen, out-of-view from the G2 patient’s vantage point, was turned off to blind the subjects.

To ensure it, all the subjects in G1 and G2 will be asked whether they are receiving a real US-guide or a placebo US-guide DN. Is placebo US-guide really effective to service the purpose of blinding the subjects? Then the data will be collected for analysis by Chi-squared test for the nominal data with using SPSS version 23 (IMB, SPSS) and an alpha is set at 0.05.

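### A chi-squared test at 0.05 on about 30 patients per arm cannot show that the placebo ultrasound blinded them

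*Protocol*

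**What the plan says.** The Methodology part of the Protocol has an item on the validity of the placebo method. It says that "all the subjects in G1 and G2 will be asked whether they are receiving a real US-guide or a placebo US-guide DN", and then poses the question that the answers should settle: "Is placebo US-guide really effective to service the purpose of blinding the subjects". The analysis follows: "Then the data will be collected for analysis by Chi-squared test for the nominal data", in SPSS, where "an alpha is set at 0.05".

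The item gives no gap between arms that would still count as adequate blinding, no interval or index, and no power for this test. The relevant size comes from the item on study subjects: "Each group will recruit 30 subjects". The sample-size item gives a smaller figure, "The number of subjects estimated for each group will be 26; total number of subjects was 78", derived for VAS and not for the blinding check.

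**The concern.** The stated question is whether the sham works. The stated tool is a test whose null hypothesis is that guesses do not differ between G1 and G2. A significant result would be evidence that the sham leaks. A non-significant result means only that no difference was detected, and with 30 per arm that can easily happen when the leak is substantial. No other result of this test could be offered in support of blinding, so the analysis cannot answer the question it is attached to.

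This matters because VAS and KOOS are patient-reported and G1 v G2 is the only contrast in which patients are blinded; G3 receives no needling. The same item says that the sham is there to remove bias and a placebo effect from the guidance. A weak check read as reassurance would lend unearned support to any claim that ultrasound guidance itself changes pain or function.

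**Working it through.** **Inputs.** From the Protocol: two arms compared (G1, G2), 30 per arm, chi-squared test, alpha 0.05. Assumed: a 2×2 table of arm by guess (1 degree of freedom); belief rates p1 (G1 guessing real) and p2 (G2 guessing real), varied over a range; no continuity correction unless stated. The Protocol gives no power for this test, so there is no figure to reproduce. The total of 78 (26 × 3) concerns VAS and has no bearing here; 26 per arm is used only as a sensitivity case.

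**1. Power for a 20-point gap.** Method: enumerate every pair of counts (x, y) with x ~ Bin(30, p1) and y ~ Bin(30, p2), and add the probabilities of the pairs where the Pearson statistic is at least 3.84.

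| G1 / G2 guessing real | Power | Missed | Power with Yates correction |
|---|---|---|---|
| 60% / 40% | 35% | 65% | 26% |
| 70% / 50% | 35% | 65% | 26% |
| 80% / 60% | 39% | 61% | 30% |
| 90% / 70% | 50% | 50% | 37% |
| 95% / 75% | 63% | 37% | 44% |
| 100% / 80% | 88% | 12% | 57% |

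Hand check at 70/50 by the normal approximation, with mean proportion 0.60: z = [0.20 × √30 − 1.96 × √(2 × 0.60 × 0.40)] / √(0.70 × 0.30 + 0.50 × 0.50) = (1.095 − 1.358) / 0.678 = −0.39, so power is about 35%, in line with the exact figure.

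With 26 per arm, uncorrected power from 60/40 to 90/70 is 29% to 47%.

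**2. What 80% power would take.** n per arm = [1.96 × √(2p̄(1−p̄)) + 0.842 × √(p1(1−p1) + p2(1−p2))]² / (p1−p2)². At 70/50: (1.358 + 0.571)² / 0.04 = 93. The other pairs give 97 (60/40), 82 (80/60) and 62 (90/70). Turned round, 30 per arm reaches 80% power only for a gap of about 30 to 35 points, depending on the base rate (90/60: 80%; 75/40: 80%).

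**3. An illustrative result.** Suppose 19/30 in G1 and 12/30 in G2 guess real.
- χ² = 60 × (19×18 − 11×12)² / (30×30×31×29) = 60 × 210² / 809,100 = 3.27, p = 0.071.
- Difference = 0.633 − 0.400 = 0.233; SE = √(0.633×0.367/30 + 0.400×0.600/30) = 0.125; 95% CI −1 to +48 points.

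The test is non-significant, yet the interval admits a gap of nearly half the patients.

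**4. Best case.** With 15/30 in each arm, the 95% CI is ±1.96 × √(0.25/30 + 0.25/30) = ±25 points. Even identical guesses would leave a gap of that size open.

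**The case against.** **The Protocol never writes that p > 0.05 means blinding is intact.** This is correct. A reader might infer that the plan will declare success on a non-significant result; the text states only the question, the test and the alpha. The criticism is therefore that the analysis has no result that could support blinding soundly, not that a written pass rule is wrong.

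**The belief rates are assumed.** Also correct. It would go too far to say that the test usually misses a 20-point gap whatever the rates. At 90/70 the odds are about even, and above that the uncorrected test detects the gap more often than not. High belief in G1 is possible, since the Protocol describes the screen as off and out of view for G2 only.

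**The question's form and timing may be settled elsewhere.** A reader might conclude that patients have only two answers and may be asked at any time. The text describes the topic of the question, not its answer options, and a chi-squared test also fits a table with a third answer. Options and timing may sit in a form or analysis plan not shown, so their absence is not counted as an error here.

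**The same table already shows each arm's proportions, and an index is no more precise.** Largely true. In the example above, the Bang index for G1 with two answers is 2 × 19/30 − 1 = 0.27, 95% CI about −0.08 to +0.61. The gain is that the uncertainty is shown by arm instead of being hidden behind a p-value.

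**The check gates nothing.** True: the VAS and KOOS analyses do not depend on it, and nothing here shows that the sham leaks or that G1 v G2 is biased. What the check does affect is what may be said about blinding in that comparison.

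**Conclusion.** The point stands in a limited form. The Protocol asks whether the placebo ultrasound blinds patients and assigns the answer to a test of difference at 0.05, with no tolerable gap and 30 patients per arm. A non-significant result would not show that the sham worked. Under assumed belief rates from 60/40 to 90/70 and the uncorrected test, a real 20-point gap goes undetected in about half to two thirds of trials; with Yates correction the miss rate over that range is 63% to 74%. Near the ceiling the uncorrected test performs better, so the size depends on rates that the Protocol does not give. The logical defect does not depend on them. It is worth correcting because it governs what the trial may claim about its only patient-blinded contrast on self-reported outcomes.

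**What to change.** State that successful blinding will not be inferred from p > 0.05. Report the guesses separately for G1 and G2, either as a Bang blinding index per arm or as proportions with their difference, each with a 95% confidence interval, and place them beside the G1 v G2 result. The chi-squared test may be kept as a description.

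When making this change, write down that the answers include a don't-know option and that the question is put early in treatment, for example after the first session, so that guesses are less driven by perceived benefit. Asking again at the end is optional; it could pick up unblinding that builds over later sessions, but those answers would be harder to separate from perceived benefit.

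The cost is one answer option, a fixed time for a question already planned, and a short calculation. Sample size, treatment and visits do not change. The downside is that with 30 per arm the intervals will be wide (roughly 20 to 25 points either side for the difference), and the statement on blinding may be less favourable than a bare p-value would suggest.

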**Benefits:**

The current study aims to investigate the effects of US-guided DN with exercise therapy on KOA patients using a comprehensive evaluation including pain level and functional ability. The findings to be obtained from this study will have a great potential to help the rehabilitation of patients with KOA in an efficient and safe manner. If US-guided DN can enhance the effectiveness of DN with exercise in improving pain and functional ability in elderly people with KOA, it potentially helps to reduce burden of total knee replacement operations to public hospitals and mortality rate. It may also release the stress of elderly patients onto the public healthcare system and to cope with the demands from the aging population in the coming future.

**Major ethical issues:**

DN or conventional acupuncture has been commonly used in patients with musculoskeletal problems. Patients may feel some dull arch feeling initially when the needling being puncture into the skin. Then patients usually will be able to adapt it. Some patients may have some unwell feeling or fainting or nausea shortly. It has been reported that the incident rate of these minor adverse events is 1.3 (0.9-1.7) per 1000 treatments; and there are no reports on serious adverse events, such as events requiring hospital admission, leading to permanent disability, or resulting in death (95% confident interval 0 to 1.1 per 10000 treatment) (MacPherson et al., 2001). If the subject feels any discomfort, the treatment will be stopped, and removal of needle immediately. The procedure will be done by a physiotherapist with accreditation in acupuncture and with experience in treating KOA by DN and clinical experience in out-patient unit for more than 10 years. The whole procedure of needling is done in supine position and the risk of fall can be minimized. Another potential risk of DN or conventional acupuncture is infection. The can be prevented by proper disinfection procedure and all the subjects’ needling points will be disinfected with the Betadine antiseptic solution [Mundipharma Pharmaceuticals LTD., Nicosia, Cyprus] and the head of US probe will be disinfected with sterile wet paper towel [Laboratories ANIOS, Lille-Hellemmes, France], and covered by a sterile 3M Tegaderm [3M, St. Paul, Minneapois, U.S.A.], and Aquagel sterile lubricating jelly [ECOLAB, Saint Paul, Minnesota, U.S.A.] as a transmission media for US scanning. All these needles being used in this study are sterile and disposable needles. The maximum of needles with the size of Dongbang Acupncture Needles at 0.3 x 40 mm [Dong Bang Acupuncture, Inc., Marsh Barton, Exeter, United Kingdom] will be seven or below. All the needles will be used once only. The risk of infection can further minimize with the exclusion criteria of any immunosuppressed diseases or under steroid treatment. From previous literatures, there were only 3 patients out of 962 patients (0.31%) who reported hypodermal bleeding and (2.1%) complained of gastrointestinal problems including nausea, stomachache, dyspepsia, and headache [Qin et al., 2015]. It may rarely happen in some cases and it will recover after rest. The procedure will be clearly explained to the subjects and the procedure will be terminated if subjects find it is too uncomfortable. Currently, the World Health Organization (2019) recommends acupuncture for over 100 diseases inducing knee pain. They encourage and support countries to identify safe and effective remedies and practices for use in public and private health services. The whole procedure of needling will be conducted in a clean working environment. The physiotherapist should clean hands and wearing sterile gloves, use disinfectant [Betadine antiseptic solution] to prepare of the needling sites and all sterile needles will be applied with an aseptic technique; and finally careful management and disposal of used needles and swabs. After the treatment finished, sterile gauze [Safe Gauze, A.R. Medicom Inc. (Asia) Ltd., Hong Kong] will be applied and pressed on the side of DN. Spot tapes sterile non-stick pad [Orison TM, Korea] will be used to cover the sites received needling treatment. The risk for septic complications and other drug related side effects related to musculoskeletal US-guided maneuvers is very low (Micu et al., 2014). Continuous monitoring the subjects’ feeling during the whole procedure, if there is any discomfort, proper management will be provided whenever necessary. It can ensure the safety and comfort and the rights of all subjects.

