**Outcomes measures:**

Primary outcomes:

1. Pain level of the KOA patients will be assessed by Visual-Analogue Scale (VAS) (Alghadir et al., 2018; Boonstra et al., 2008)
2. The functional mobility of the KOA patients will be assessed by the Knee Injury and Osteoarthritis Outcome Score (KOOS)-short form (Roos et al., 2003; Cheung, Ngai and Ho., 2016)

Secondary outcomes:

1. Compliance of Exercise

Exercise compliance for participants was assessed at 4 weeks and 8 weeks by an independent assessor. The duration of exercise was assessed by hour per week. (Appendix VII).

1. Medication Utilization During the Study Period

The use of pharmacological interventions for participants was assessed at baseline, 4 weeks, and 8 weeks.

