Inclusion criteria were based on previous relevant studies (Itoh et al., 2008; Sánchez-Romero et al., 2018). Inclusion criteria were as follows: 1) >50 to 80 years old, 2) referred with a diagnosis of KOA (i.e., primary KOA fulfilling the American College of Rheumatology criteria developed by Altman et al. (1986) (at least three out of six) for clinical and radiographical diagnostic KOA 3) presenting with anterior and/or medial knee pain with 2-3 local tender spots, 4) crepitus, 5) functional limitations caused by KOA over a period of at least six months, 6) stiffness <30 minutes, 7) KL scale (Petersson et al.,1997) of grade I to grade III; and 8) able to read Chinese and communicate in Cantonese based on literacy.

Exclusion criteria, made with reference to previous studies (Itoh et al., 2008; Sánchez-Romero et al., 2018), were: 1) having knee pain less than 6 months; 2) having other musculoskeletal diseases associated with knee pain (e.g., referred pain from the low back or posterior or lateral knee pain or co-existing pain over the other limb); 2) suffering from acute inflammation, diffuse tenderness upon palpation test, bone marrow lesion, severe joint deformity with X-rays revealing a grade IV in the KL scale (Petersson et al., 1997), coagulation disorders, metabolic, or neuropathic arthropathies, immunosuppressed or systematic disease; 3) having severe concomitant illness that might affect the clinical outcomes of this study, 4) contraindications to DN including pregnancy, malignancy, fear of DN; 5) having recent treatment involving acupuncture or DN therapy or non-pharmacological intervention (e.g., physiotherapy) within a month prior to the start of the study; 6) inability to answer questionnaires and non-responsiveness towards the assessor; 7) having a wound or pressure sore or skin problems or skin allergy, including an allergy to iodine; and 8) having a history of injecting steroids.

Participants will be provided with written information sheets and verbal explanations. Written consent will be signed. They can withdraw from the study at any time. All the adverse effects, if any, will be recorded and reported in this study. The group allocation and data will be concealed in a password-protected computer file only accessible by the principal investigator.

Table 1: Participants flow chart:

Recruit from advertisements on social media and assessed by orthopedic surgeon for eligibility of KOA

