Appendix IV

Data collection form

| Case identity | Date of assessment | Age | Gender | | | BMI | | Unilateral/Bilateral knee pain | | Duration of knee pain | Any injury |
| --- | --- | --- | --- | --- | --- | --- | --- | --- | --- | --- | --- |
|  |  |  | M / F | | | Height: M  Weight: Kg | | R ______  L ______  Both ___ | | ___months | (Y / N) |
| Severity of pain (VAS) | KOOS-Pain score | KOOS-  symptoms  score | KOOS_ADL score | | | Remarks (any any discomfort or side effects): | | | | | |
| _____ mm | ______/36 | ______/28 | ______/68 | | |
|  |  |  |  | | |
| Number of needle used  ( ) | Areas applied dry needling or acupuncture  Oblique/perpendicular insertion: / | | | | |  | Nausea/faint/ hypodermal bleeding others:  _______________________________ | | | | |
| Compliance of exercises: |  | | | | XR: KL scale: Grade 0 / I / II /III /IV | | | | | | |
| Tablets of medication |  | | | Number of tender spots: | | | | | Depth of insertion (mm): | | |
| Ultrasound findings | Patient code: ___________  Real US-dry needling: Y/N  Findings: __Power Doppler of blood flow increased/decreased (neovascularity +/-)  Mucoid degeneration/increased thickness/hypoechogenecicity/hyperechogenecity  __________________________________________________________________________________  __________________________________________________________________________________  __________________________________________________________________________________ | | | | | | | | | | |
| Location of dry needling | [figure not shown]  L medial  R medial | | | | | | | | | | |

Key: Q= quadriceps strength, H= hamstrings strength, ROM=range of motion, R= right and L= left, M=male, F=female, Y= yes and N= no, MMT: manual muscle testing

Scales: mm= minimeter, N=newton, 0 is degree of angle

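### The ethics section counts current steroid treatment among the exclusions that limit infection risk, but the exclusion list names only past steroid injections

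*Protocol*

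**What the plan says.** The Major ethical issues section of the protocol treats infection as a potential risk of needling. Alongside the aseptic measures (skin antiseptic, a disinfected and covered probe, sterile single-use needles) it gives a further protection: "The risk of infection can further minimize with the exclusion criteria of any immunosuppressed diseases or under steroid treatment". The sentence refers to the exclusion criteria as already settled and attributes two things to them: immunosuppressed disease and being under steroid treatment.

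The criteria themselves are in Methodology, Study subjects. The second of the two items numbered 2 includes "metabolic, or neuropathic arthropathies, immunosuppressed or systematic disease". The only item that mentions steroids is the last: "8) having a history of injecting steroids".

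Medication is dealt with in two other places. Under Outcomes measures it is a secondary outcome: "The use of pharmacological interventions for participants was assessed at baseline, 4 weeks, and 8 weeks". The data collection form in Appendix IV has a field labelled "Tablets of medication".

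**The concern.** The risk section relies on an exclusion that the screening list does not fully contain. Being under steroid treatment describes what a patient is taking now, by any route. A history of injections describes a past event by one route. Someone taking oral steroids today who has never had an injection fits the first description and not the second.

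What is at stake is patient safety and consistent eligibility. Those who read the risk section would take it that such patients are kept out, while whoever screens from the list has no item telling them to do so. The two needling arms are where this matters, since G3 receives exercise and education without needles.

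**Working it through.** No figure in the protocol needs reproducing here. The check compares the stated safeguard with each exclusion item that could carry it.

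**The safeguard against the list**

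| Part of the safeguard (Major ethical issues) | Counterpart in the exclusion list | Match |
| --- | --- | --- |
| Immunosuppressed disease | Second item 2 | Yes |
| Under steroid treatment (current, no route given) | Item 8, past injections only | Partial |

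Item 8 is stricter than the ethics section for injected steroids, because any past injection excludes. For steroids taken by another route it does nothing.

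**Could another item close the gap?**

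- Second item 2 (immunosuppressed or systemic disease) may catch some oral users through the underlying illness, or because the screener regards them as immunosuppressed. It does not name steroid treatment, and the ethics section lists steroid treatment separately from immunosuppressed disease.
- Item 3 (severe concomitant illness) depends on whether the illness could affect the clinical outcomes, not on infection risk.
- Item 4 reads "contraindications to DN including pregnancy, malignancy, fear of DN". The wording leaves the list open, but steroid use is not among the examples.
- Item 5 reads "having recent treatment involving acupuncture or DN therapy or non-pharmacological intervention", with a one-month window. Drug treatment is outside it.
- The medication outcome records use without restricting it. The Appendix IV field asks about tablets and has no steroid entry, so neither serves as a screening check.

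**Counts**

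- Exclusion items as numbered: 1, 2, 2, 3, 4, 5, 6, 7, 8, which makes 9 items. Items naming steroids: 1 (injected). Items naming current or oral steroid treatment: 0.
- Patients to be needled: 30 (G1) + 30 (G2) = 60 of 90.
- Needles per needled patient: if the maximum of seven applies to each session, 7 × 4 weekly sessions = 28 at most. The protocol does not say outright that the maximum is per session, so this is an assumption.

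These counts describe exposure to the procedure. They do not estimate infection risk or the number of steroid users, for which the protocol gives no data.

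**The case against.** The strongest reply is that nothing was dropped. The ethics sentence points back to the exclusion list; the list has one immunosuppression item and one steroid item, and the sentence mentions one of each. On that reading, being under steroid treatment is loose shorthand for item 8. This is possible, but it does not fit the words well: the sentence speaks of current treatment and limits it to no route. Even if it is right, the ethics section then claims more than the list delivers, and one of the two texts needs correcting.

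A second reply is that the patients at real risk are mostly covered already. Immunosuppressed can describe a patient's state as well as a disease, many conditions that call for long-term oral steroids are systemic, item 4 is open-ended, and patients come with a doctor's referral and are assessed by an orthopaedic surgeon. Much of this stands, and it makes the remaining group narrow. But each of these routes depends on the screener's judgement, and none names steroids.

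It is also fair to say that Appendix IV is a data collection form and a separate screening form may exist, and that the counts of patients and needles show no harm. Both points stand. The concern rests on the mismatch between the two texts, not on those counts.

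**Conclusion.** The point holds, at low severity. Current steroid treatment by a route other than injection is not expressly excluded, although the ethics section presents steroid treatment as an exclusion that lowers infection risk. The conclusion rests on reading that phrase as it stands, without restricting it to injections. It does not claim that every oral steroid user would get through, since some would be stopped under other items. The number who would be enrolled cannot be derived from the protocol and may be near zero. The exclusion is an extra layer on top of asepsis, and the mismatch has no bearing on sample size, power or analysis.

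**What to change.** Add current systemic (including oral) steroid treatment to the exclusion list beside item 8, and put the matching question to patients at screening. The list applied would then carry the safeguard that the ethics section claims. The cost is one line of protocol text, one screening question and at most a few patients lost at screening.

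If the sponsor did not mean to exclude oral users, the alternative is to reword the sentence in Major ethical issues so that it claims only what item 8 provides. That would make the two texts agree but would add no protection.
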